### Study assessments

2.4

All enroled subjects will be assessed until month 12 for the evaluation of efficacy and safety endpoints, including interim treatment visits (Figure 1). Clinical response will be evaluated based on in‐person assessments and photographic images of the treated hallux, both in terms of the affected nail area and nail length. Mycology testing will be performed at baseline, day 84 (month 3), day 168 (month 6), day 252 (month 9) and day 336 (month 12).

Incidence of adverse events (AEs) will be recorded throughout the entire study period; each AE will be graded based on severity (mild, moderate, severe) and relatedness to the study intervention. The investigator will deem an AE as ‘expected’ if it's consistent with previous reports in the literature,^10^, ^11^, ^18^ which includes local application site reactions such as pain, bruising, heat sensitivity and tingling. Burns, blisters, or nail disfigurement will be considered as ‘unexpected’ AEs. Any new clinically relevant findings deemed by the investigator will be reported as an AE. Patients will be asked to report their pain level—categorised as none, mild, moderate or severe—before treatment, during treatment, and 10‐min post‐treatment. Additionally, patient‐reported outcomes (PROs) will be recorded at pre‐specified timepoints of which patients will be asked to rate (a) how their daily activities are affected, (b) how their lifestyle activities (e.g. sports, hobbies) are affected and (c) how their mood is affected.

Subjects who wish to discontinue from treatment will be asked to complete all remaining study assessments as planned. The principal investigator may withdraw a subject from the study if there is significant protocol non‐compliance, AEs or other medical conditions such that the continued study participation would not be in the interest of the subject, or subject meeting the exclusion criteria during the study period. If a subject fails to return for 2 scheduled visits, and is unable to be contacted (through multiple telephone calls and letters), the site staff will make a reasonable effort to ascertain reason(s).

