### Study participants

2.1

Adult patients presenting with DSO of one hallux, with 20%–75% involvements of the nail area, nail thickness of ≤3 mm and no area of infection <3 mm from the proximal nail fold, will be enroled and allocated to treatment. Inclusion and exclusion criteria are summarised in Table 1. No eligibility waivers will be permitted.

**TABLE 1 ski2455-tbl-0001:** Patient eligibility criteria.

Inclusion criteria
Provide written informed consent Aged ≥18 years Not pregnant or breastfeeding Subject presenting with distal subungual onychomycosis of one hallux Mycology‐positive diagnosis confirmed by the detection of a dermatophyte One hallux as a treatment target with 20%–75% nail area affected One hallux as a treatment target with a thickness of ≤3 mm No area of infection <3 mm from the proximal nail fold No more than 4 toenails showing visual signs of onychomycosis including the treatment target Subject agrees not to take any oral or topical antifungal treatments for the duration of the study Subject able to undergo study assessments

Exclusion criteria

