Subject presenting with proximal subungual onychomycosis or superficial white onychomycosis Hallux designed as the treatment target shows disease involvement of the lunula Non‐onychomycotic dystrophy presenting as parallel lines, small pinpoint depressions, brown spots, black or brown linear streaks, complete yellowing of all nails without textual changes, green debris below the nail or notches in the nail margin Causative fungal agent belonging to rare species or non‐fungal organisms such as non‐dermatophyte mould, *Candida*, or bacteria ‘Spike’ of onychomycosis extending to <3 mm away from the eponychium Presence of dermatophytoma Type I or II diabetes mellitus Peripheral vascular disease Recurrent cellulitis Lymphatic insufficiency Immunocompromised Severe moccasin tinea pedis Any uncontrolled condition which, in the opinion of the investigator, may put the subjects at undue risk of adverse effects during the study Exhibit an increased risk of bacterial infections due to skin breakdown caused by a fungus Co‐morbidities known to induce nail changes including psoriasis and lichen planus Trauma due to ill‐fitting shoes, running or overly‐aggressive nail care Regularly scheduled podiatric/nursing nail care History of recent toenail surgery with residual disfigurement Recent topical onychomycosis treatments ≥3 months prior to study treatment or oral onychomycosis treatments ≥6 months prior to study treatment Implantable cardioverter defibrillator, pacemaker or other implantable devices Metal implants at or near the treatment site History of intolerance or allergy to microwave therapy History of any topical metallic or ionic treatment within the last 6 months Current participation of another non‐observational trial or within the last 30 days

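### Investigator withdrawal for meeting an exclusion criterion makes no exception for worsening of the target nail, so a failing patient's later data could be lost

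*Protocol article*

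**What the plan says.** Section 2.4 (Study assessments) gives the principal investigator discretion to withdraw a patient from the study. The grounds are marked non-compliance, adverse events or other medical conditions that make staying in against the patient's interest, "or subject meeting the exclusion criteria during the study period". No criterion is exempted.

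The exclusion criteria in Table 1 (section 2.1) include:

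- "Hallux designed as the treatment target shows disease involvement of the lunula"
- a spike "of onychomycosis extending to <3 mm away from the eponychium"
- "Presence of dermatophytoma"

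Other limits on the target nail appear only as inclusion criteria: affected area of 20% to 75%, no infection within 3 mm of the proximal fold, and "One hallux as a treatment target with a thickness of ≤3 mm".

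On follow-up, section 2.4 states in general that "All enroled subjects will be assessed until month 12 for the evaluation of efficacy and safety endpoints". Its retention sentence reads "Subjects who wish to discontinue from treatment will be asked to complete all remaining study assessments as planned". Section 2.2 offers retreatment to non-responders at months 6 and 9, and asks those who decline to return at months 9 and 12. Mycology is scheduled at baseline and on days 84, 168, 252 and 336.

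**The concern.** For most exclusion criteria (a new implant, cellulitis, immunocompromise) such a clause is ordinary patient protection. The three criteria above are different. A nail that was free of them at day 0 and shows them later has worsened under treatment, unless the finding was missed at baseline. Lunula involvement and a proximal spike run opposite to the clear-nail measure, which is distance from the proximal fold. The reason for leaving observation can then be the outcome itself.

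The results exposed are the mean clear-nail increase (section 2.8), mycological and effective cure at months 6, 9 and 12 (section 2.6), and the per-protocol results. An analysis rule can classify a withdrawn patient as a failure. It cannot supply nail lengths, areas or mycology results that were never obtained. Any distortion would tend to favour the device.

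**Working it through.** There is no figure in the article to reproduce: section 2.8 says no sample size calculation was made. The check is textual first, then a range under stated assumptions.

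**1. Reach of the clause.** It invokes exclusion criteria only. Lunula involvement, a spike under 3 mm and dermatophytoma are therefore caught. A broad front crossing 3 mm, more than 75% of the area affected, or thickness above 3 mm breaches inclusion limits only and is not caught.

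**2. Whether other text closes the gap.**

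- The retention sentence applies to patients who choose to stop treatment, not to those the investigator withdraws.
- The month 12 statement is a general intent. It does not limit the specific power to withdraw from the study.
- Section 2.2 handles non-response from month 6 onward, so it does not cover earlier worsening, and it does not restrict the clause.

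**3. Scheduled mycology lost.** Section 2.4 schedules four post-baseline tests. The month 3 test feeds no cure endpoint listed in section 2.6.

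| Withdrawal | Tests lost | Of these, tests that feed a cure endpoint |
|---|---|---|
| before day 84 | 4 | 3 |
| days 84 to 168 | 3 | 3 |
| days 168 to 252 | 2 | 2 |
| days 252 to 336 | 1 | 1 |

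**4. Size.** Section 4 reports 39 enrolled, so 39/3 = 13 per arm under 1:1:1 allocation. Assumed: 0 or 1 such withdrawal per arm, because section 1 calls the disease slowly progressive. With 0 there is no effect. With 1, suppose the patient contributes nothing at the visit analysed.

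*Mean clear-nail increase.* Let m be the mean of the other 12 and x the change the withdrawn nail would have shown (both assumed). The overstatement is m − (12m + x)/13 = (m − x)/13.

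- m = 1, x = −1: 2/13 = 0.15 mm
- m = 3, x = −1: 4/13 = 0.31 mm (3.00 reported against 35/13 = 2.69)
- m = 5, x = −3: 8/13 = 0.62 mm

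*Cure proportion among those measured* (cure counts assumed, withdrawn patient not cured):

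- 2/13 = 15.4% becomes 2/12 = 16.7%: +1.3 points
- 5/13 = 38.5% becomes 5/12 = 41.7%: +3.2 points
- 8/13 = 61.5% becomes 8/12 = 66.7%: +5.1 points

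For scale, the standard error of one arm at 5/13 is √(0.385 × 0.615/13) = 13.5 points. If the withdrawn patient is kept in the denominator as a non-responder, 5/13 stays 5/13 and the shift is 0.

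**The case against.** The clause is permissive and of a common kind. The design otherwise follows failures: it offers them retreatment and invites them back. Nothing suggests the clause is aimed at treatment failure. The article condenses a fuller protocol that may keep withdrawn patients in assessment, and intention-to-treat is named as an analysis population. The worsening that prompts withdrawal would itself be on record. Withdrawal may also serve the patient, because participants agree to forgo antifungals and oral agents are barred, so leaving the study can be the route to drug treatment.

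Most of this stands as a limit on weight. It does not remove the point, because the article states a rule about who stays under observation, and that is not a detail left to an analysis plan. The need for drug treatment is a real objection to a bare ban on withdrawal, so the remedy has to provide for rescue. It also has to cover the separate ground of adverse events or other medical conditions, under which the same patient could be withdrawn.

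A reader might infer more than this:

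- **That the results are biased, or that the comparison of regimens is.** With assumed responders of 9/15, 5/15 and 4/15, the chi-square test gives p = 0.143. Dropping three failures from the first arm only (9/12, 5/15, 4/15) gives p = 0.027. That needs three such withdrawals in one arm, none in the others, and no counting as non-response. The documents give no ground for any of these.
- **That every nail breaching an eligibility limit can be withdrawn.** The clause does not invoke the inclusion limits.

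**Conclusion.** The point holds as a minor weakness in a stated rule. Section 2.4 permits, but does not require, withdrawal from the study for three findings that can be failure of the treated nail, and nothing else in the article keeps such a patient in assessment. If the clause is used this way, the mean clear-nail increase and the cure proportions among those measured could look slightly better than they are. The likely shift is well inside the sampling error of one arm. That judgement rests on the assumed 0 or 1 withdrawal per arm, the assumed nail changes and cure counts, and a full protocol that adds no further retention rule. The co-primary responder proportions are unaffected if intention-to-treat counts these patients as non-responders. No difference between regimens is claimed.

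**What to change.** Amend section 2.4, at low priority, to state that:

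1. Lunula involvement, a spike less than 3 mm from the eponychium, or dermatophytoma arising in the target nail after day 0 is a ground to stop microwave sessions but not to withdraw the patient from the study.
2. Every patient whose treatment the investigator stops, on any ground including adverse events, is asked to attend the remaining scheduled assessments unless consent is withdrawn.
3. Rescue antifungal therapy is then allowed and recorded. A patient who receives it counts as a non-responder (not cured) from that point, and later measurements are reported as post-rescue.

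The cost is a few sentences, since the visits are already scheduled. The downsides are slightly less favourable results and some post-rescue data that need separate handling.

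Only patients still in follow-up benefit. Taking the close of enrolment as 31 May 2024, these are patients whose day 0 fell after 30 June 2023 (336 days earlier). Under an assumed even rate from March 2023 to May 2024, that is 11/15 × 39 = 28.6, about 29 patients. The rate may not have been even, because an amendment approved in June 2023 aimed to raise it. The number falls to none by about 2 May 2025, or 14 days later with the month 12 visit window. The clause should also not be carried into the pivotal trial that this pilot is meant to inform.

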### Primary endpoints

2.5

The co‐primary endpoints include (a) an acceptable safety and tolerability profile at the end of month 6 (day 168 ± 7 days) defined by treatment adherence with minimal mild‐to‐moderate treatment‐related AEs (expressed as frequencies per category), which resolve before further treatments with no sequelae, and (b) proportion of subjects achieving the following endpoints at month 3 (day 84 ± 7 days) and month 6 (day 168 ± 7 days): month 3—US FDA definition of ‘temporary increase in clear nail’ with evidence of nail improvements defined as an increase in clear nail measured in distance from the proximal nail fold or an increase of the clear nail area; month 6—achieving either (1) ≥ 6 mm increase in clear nail measured in distance from the proximal nail fold, (2) an additional 60 mm^2^ of the treated nail area achieving clearance with evidence of outward growth or (3) complete clearance if less than 6 mm of the distal nail was involved at baseline.

### Secondary endpoints

2.6

Secondary safety endpoints include (a) the maintenance of an acceptable safety and tolerability profile beyond the end of month 6 (day 168 ± 7 days) for patients undergoing retreatment defined by treatment adherence with minimal mild‐to‐moderate treatment‐related AEs (expressed as frequencies per category), which resolve before further treatments with no sequelae, (b) frequency of ‘expected’ AEs, (c) incidence of AEs that differentiate ‘target’ and ‘non‐target’ toenails, (d) comparison of pain levels during and after treatment and (e) comparison of pain levels as a function of the number of treatments and treatment frequency.

Secondary efficacy endpoints include (a) proportion of subjects achieving at least one of the two criteria—a ≥3 mm increase in clear nail measured in distance from the proximal nail fold or a ≥30% increase in the total nail area achieving clearance with evidence of outward growth —at the end of month 6 (day 168 ± 7 days), (b) proportion of subjects achieving improved PROs, (c–e) proportion of subjects achieving mycological cure (negative mycology testing results) achieved at the end of, (c) month 6 (day 168 ± 7 days), (d) month 9 (day 252 ± 14 days) and (e) month 12 (day 336 ± 14 days) and (f,g) proportion of subjects achieving effective cure (≤10% of the total nail area affected with mycological cure) achieved at the end of (f) month 6 (day 168 ± 7 days), (g) month 9 (day 252 ± 14 days) and (h) month 12 (day 336 ± 14 days).

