### Study intervention

2.2

On day 0, patients will be randomized (1:1:1) to one of three treatment groups (Groups A–C) based on a computer‐generated randomisation schedule generated prior to the start of the study (Figure 1). Group A will undergo nine treatment sessions, which includes the first session at day zero followed by four weekly sessions then four monthly sessions. Group B will undergo 7 treatment sessions, which includes the first session at day 0 followed by sessions every 2 weeks for 2 sessions then 4 monthly sessions. Group C will undergo 12 treatment sessions, which includes the first session at day 0 followed by sessions every 2 weeks.

Non‐responders at the end of the month 6 visit (day 168) or month 9 visit (day 252) as judged by the US FDA recommended endpoint (i.e., “temporary increase of clear nail”) will be given the option to undergo retreatment once per month for 3 months up to month 9 or month 12, respectively (Figure 1).^13^ Subjects who do not wish to undergo retreatment will be asked to return for month 9 and month 12 visits.

Tinea pedis is a common co‐infection seen in onychomycosis patients^17^; in this study, patients presenting with concomitant tinea pedis, at the investigator's discretion, may be provided with topical antifungal agents for treating affected skin areas. Toenails will be strictly avoided. No local anaesthetic, petroleum jelly nor metallic‐based topical treatments (e.g., aluminium chloride, silver nitrate) are to be used in the toenail areas during this study. Concomitant use of oral antifungal agents is not permitted.

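### Secondary safety endpoint (a) describes maintained safety after month 6 by adverse-event frequencies that are not adjusted for a much smaller number of sessions

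*Protocol article*

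**What the plan says.** Under Primary endpoints, the safety co-primary is "an acceptable safety and tolerability profile at the end of month 6". It is defined by adherence and by few, at most moderate, treatment-related AEs that clear up before the next treatment and leave no lasting effect. AEs are given as frequencies in each category.

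Under Secondary endpoints, safety endpoint (a) is "the maintenance of an acceptable safety and tolerability profile beyond the end of month 6". It repeats the same definition and the same way of expressing AEs, but only for patients who are retreated.

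Study intervention sets the exposure in the two periods. For the initial course:
- "Group A will undergo nine treatment sessions, which includes the first session at day zero followed by four weekly sessions then four monthly sessions".
- For Group B the total is 7: one at the start, two more at two-week spacing, and four at monthly intervals.
- "Group C will undergo 12 treatment sessions, which includes the first session at day 0 followed by sessions every 2 weeks".

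After that, non-responders at month 6 or month 9 "will be given the option to undergo retreatment once per month for 3 months up to month 9 or month 12, respectively". Those who decline are asked only to attend the month 9 and month 12 visits.

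Data analysis describes AE tabulations and names no per-session denominator.

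**The concern.** The word maintenance invites the reader to set the profile after month 6 beside the profile at month 6. The two are not on a common exposure basis, because patients receive far fewer sessions in a retreatment round than in the initial course. An AE count, or a percentage of patients with an AE, depends on how many sessions each patient had. A lower figure after month 6 could then be read as safety maintained or improved when it reflects only fewer sessions.

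Two further differences point to the same need for a clear basis. Retreatment sessions are all monthly, whereas sessions are weekly early in Group A and two-weekly early in Group B and throughout Group C, so an AE has more time to resolve before the next session. The later set also contains only non-responders who accepted the offer.

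The stake is modest but real. The pilot is meant to inform a pivotal trial, and tolerability of longer treatment is what this endpoint is there to describe.

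**Working it through.** **Session counts in the plan.** These can be rebuilt from Study intervention, taking a month as 28 days:
- Group A: 1 + 4 + 4 = 9, last session about day 140.
- Group B: 1 + 2 + 4 = 7, last session about day 140.
- Group C: 12 two-weekly sessions, days 0 to 154.

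The stated 9, 7 and 12 are reproduced, and all sessions fall before day 168.

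**Sessions after month 6.** The text gives "retreatment once per month for 3 months up to month 9 or month 12, respectively", so about 3 per round. Six requires non-response at both month 6 and month 9 and acceptance of both rounds. The text allows this but does not say it. The schedule figure is not visible to this review.

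**Expected AE count at unchanged risk per session.** The ratio of later to initial count is the ratio of session numbers:
- One round: 3/7 = 0.43 (B), 3/9 = 0.33 (A), 3/12 = 0.25 (C).
- Two rounds: 6/7 = 0.86 (B), 6/9 = 0.67 (A), 6/12 = 0.50 (C).

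**Patients with at least one AE.** With a constant, independent risk q per session and k sessions, the probability is 1 − (1 − q)^k. The document gives no value for q, so a range is assumed.

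| q (assumed) | 3 sessions | 6 sessions | B: 7 | A: 9 | C: 12 |
|---|---|---|---|---|---|
| 5% | 14% | 27% | 30% | 37% | 46% |
| 10% | 27% | 47% | 52% | 61% | 72% |
| 20% | 49% | 74% | 79% | 87% | 93% |

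For example, at q = 10%, 1 − 0.9³ = 0.271 and 1 − 0.9⁷ = 0.522.

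**Rise in risk needed to reach the initial percentage.** Solve 1 − (1 − q′)^k = 1 − (1 − q)^m, where m is the number of initial sessions, which gives q′ = 1 − (1 − q)^(m/k). At q = 10%:
- k = 3: q′ = 21.8% (B), 27.1% (A), 34.4% (C), which is 2.2, 2.7 and 3.4 times q.
- k = 6: q′ = 11.6% (B), 14.6% (A), 19.0% (C), which is 1.2, 1.5 and 1.9 times q.

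**Per-session rate.** Expected events are kq. Divided by k sessions this is q in both periods, so the exposure effect disappears.

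**Opt-in selection.** A per-session rate does not remove this. Suppose half the patients have q = 5% and half q = 20%, so the initial rate is 12.5%.
- If 10% of the low-risk and 50% of the high-risk patients decline, the later rate is (0.45 × 5% + 0.25 × 20%)/0.70 = 10.4%.
- If the declining proportions are reversed, it is (0.25 × 5% + 0.45 × 20%)/0.70 = 14.6%.

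Both cases are invented. They show that the direction depends on who declines, which the document does not tell us.

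**The case against.** The strongest reply is that no before-and-after comparison is written. Endpoint (a) reapplies an absolute definition to retreated patients, so maintenance may simply mean that the profile is still acceptable. Data analysis describes tabulation and nothing between periods. This stands in part: the comparison is implied by the word and not specified. Even read as an absolute standard, though, few AEs over about 3 sessions is easier to meet than few AEs over 7 to 12.

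Second, no denominator is fixed, and a condensed article may leave it to a fuller document. A reader might infer that rates must fall by construction. The text does not support that: a per-session rate would not fall from lower exposure, and a count could still rise if risk grew enough with repeated treatment. The point holds for counts and per-patient percentages, which are the ordinary reading of frequencies.

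Third, a reader might infer that the endpoint would show maintained safety whatever the true risk. That goes too far. Severity, resolution and lasting effects are part of the definition, and one severe event would count against it however few sessions were given. Secondary safety endpoint (e) also relates pain to the number and frequency of treatments. That covers pain but not other AEs.

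Fourth, selection is declared openly: the endpoint is for retreated patients, who "will be given the option to undergo" more sessions. A reader might infer that patients with a painful first course drop out and flatter the result. That is plausible, but nothing in the document shows it.

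Finally, two rounds narrow the gap, almost closing it against Group B.

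**Conclusion.** The point holds in a limited form. Unadjusted AE counts or per-patient frequencies after month 6 are not comparable with those of the initial course and would tend to look lower at unchanged risk per session. For one round of about 3 sessions the expected count is 25–43% of the initial one. At an assumed 10% per session, 27% of patients would have an AE, against 52% (B), 61% (A) and 72% (C). For two rounds the difference is small against Group B (47% against 52%) and larger against Group C (47% against 72%).

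These figures assume a constant, independent risk per session, full attendance and a frequency not expressed per session. The direction of any selection effect is unknown. The priority is minor: the endpoint is secondary and descriptive, no test or decision rule hangs on it, and it concerns a subset of the 39 patients enrolled.

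**What to change.** For secondary safety endpoint (a), report treatment-related AEs per treatment session delivered, by category and severity. Place beside this the per-session rate of the same retreated patients during their initial course, as a descriptive comparison within patients. State how many eligible non-responders declined retreatment, with their initial-course AE rate, so that a reader can judge selection.

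This changes the analysis wording only. Treatment procedures already records dose, duration and repetitions at each session, and Study assessments records AEs throughout, so no visit, procedure or treatment rule is affected. The cost is that estimates in a small subset will be imprecise, and the retreatment figure may look less favourable than an unadjusted one.

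### Secondary efficacy endpoint (a) has no complete-clearance route, so a small group of eligible nails (under 3 mm deep and under 30% affected) could clear fully, pass the month-6 primary endpoint and fail the more lenient secondary one

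*Protocol article*

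**What the plan says.** All references are to the Protocol article.

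- **2.5 Primary endpoints, month 6.** Any one of three routes suffices: (1) at least a "6 mm increase in clear nail measured in distance from the proximal nail fold"; (2) an additional 60 mm² of clear nail with outgrowth; (3) "complete clearance if less than 6 mm of the distal nail was involved at baseline".
- **2.6 Secondary endpoints, efficacy (a), month 6.** The measure is the "proportion of subjects achieving at least one of the two criteria". The first is at least a "3 mm increase in clear nail measured in distance from the proximal nail fold". The second is at least a 30% "increase in the total nail area achieving clearance with evidence of outward growth". No third route is given, and the base of the 30% is not stated.
- **2.1 Study participants, Table 1.** "One hallux as a treatment target with 20%–75% nail area affected". Infection must also stay at least 3 mm away from the proximal nail fold. No minimum depth of distal involvement is set.

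**The concern.** Primary route (3) exists because a nail with little distal involvement cannot gain 6 mm however well it responds. The secondary endpoint halves the length threshold to 3 mm, which shrinks that problem but does not remove it. A nail with under 3 mm involved cannot gain 3 mm, and if it also has under 30% of its area affected it cannot gain 30 percentage points of nail area. For such a nail the best possible result is scored as a failure.

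Two things are at stake. First, a reader will take 3 mm or 30% as a relaxed form of 6 mm or 60 mm² and expect every fully cleared primary success to count on the secondary as well. Second, the arms are small. With 39 enrolled (4 Trial status), there are about 39/3 = 13 per arm, so one misclassified complete clearance moves an arm's rate by 1/13, about 8 percentage points, in a trial meant to inform the choice of dosing frequency.

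**Working it through.** The article states no figure to reproduce here, so the check is of the logic and geometry of the rules.

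**Inputs from the article:** thresholds of 6 mm and 3 mm; the 30% area rule; primary route (3) for under 6 mm; involvement of 20% to 75%; infection at least 3 mm from the proximal fold; 39 enrolled. **Assumed, because not in the article:** nail length L, taken as 10 to 15 mm, and a rectangular plate with a full-width distal band, so that affected share a = d/L for baseline depth d.

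**Step 1: when does a fully cleared nail fail the secondary?** On full clearance the length gain is d and the cleared share is a. The nail fails the length rule if d < 3 mm. It fails the area rule according to how the 30% is read:

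- percentage points of total nail area: fails if a < 30%;
- relative to baseline clear area: fails if a/(1 − a) < 0.30, that is a < 0.30/1.30 = 23.1%;
- relative to baseline affected area: the gain is 100%, so it never fails.

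Any nail with d < 3 mm has d < 6 mm, so if fully cleared it meets primary route (3). The conflict therefore needs d < 3 mm together with 20% ≤ a < 30% (first reading) or 20% ≤ a < 23.1% (second reading).

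**Step 2: an example.** L = 12 mm, d = 2.7 mm. Then a = 2.7/12 = 22.5%, and the infection stops 12 − 2.7 = 9.3 mm from the fold, so the nail meets the area and proximal-distance criteria. Fully cleared, it meets primary route (3). The length gain of 2.7 mm is below 3 mm. The area gain is 22.5 percentage points, or 22.5/77.5 = 29.0% relative to clear area, both below 30%. The secondary fails on either reading.

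**Step 3: which nail lengths allow it?** With a ≥ 20%, d ≥ 0.20L. Combined with d < 3 mm this requires L < 3/0.20 = 15 mm. The conflicting depths run from 0.20L to the smaller of 3 mm and 0.30L (first reading) or 0.231L (second reading). The eligible depths under primary route (3) run from 0.20L to 6 mm.

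| L (mm) | Eligible depths under route (3), mm | Conflict, first reading | Conflict, second reading |
|---|---|---|---|
| 10 | 2.0 to 6 | 1.0/4.0 = 25% | 0.31/4.0 = 8% |
| 12 | 2.4 to 6 | 0.6/3.6 = 17% | 0.37/3.6 = 10% |
| 14 | 2.8 to 6 | 0.2/3.2 = 6% | 0.2/3.2 = 6% |
| 15 or more | 3.0 or more to 6 | 0 | 0 |

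These are shares of a depth range, not of patients.

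**Step 4: a ceiling on patients.** Assume further that involvement is spread evenly over 20% to 75%. The share of patients who could meet neither secondary route (first reading) is (min(0.30, 3/L) − 0.20)/0.55:

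- L = 10: 0.10/0.55 = 18%, 7.1 of 39. If the 3 mm proximal limit is applied, it caps involvement at 7/10 = 70% and gives 0.10/0.50 = 20%, 7.8 of 39.
- L = 12: 0.05/0.55 = 9%, 3.5 of 39.
- L = 14: 0.0143/0.55 = 2.6%, 1.0 of 39.
- L = 15 or more: 0.

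On the second reading, 10 mm and 12 mm both give 0.0308/0.55 = 5.6%, 2.2 of 39. A patient is misclassified only if the nail also clears completely by month 6. At assumed complete-clearance rates of 10% to 25%, the first-reading counts become 0.4 to 0.9 patients at 12 mm and at most 7.8 × 0.25 ≈ 2 at 10 mm.

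**Step 5: does a third route close the gap?** Yes. A fully cleared nail with d ≥ 3 mm already meets the length rule, and one with d < 3 mm would meet the new route. An extra condition on area below 30% is not needed.

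**The case against.** The strongest case against is that the affected group is very narrow and full clearance is credited elsewhere. Primary route (3) counts it; effective cure at month 6 counts it when mycology is negative; and mean gains in clear length and area are analysed as continuous measures (2.8 Data analysis). The retreatment option in 2.2 is tied to the FDA endpoint, not to this one. Nothing in the article says that secondary (a) must contain the primary, and a fixed-size response measure is a legitimate choice. All of this stands, and it is why the point is minor. It does not explain why a fully cleared nail should be scored as a failure on the easier of two related endpoints.

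Four stronger readings are tempting and are not supported:

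- *Every fully cleared nail with limited involvement fails the secondary.* Fully cleared nails 3 to under 6 mm deep meet the 3 mm rule and pass both endpoints.
- *Some 18% of patients are misclassified.* That figure is a ceiling under assumed nail length, band shape and spread, on one reading of the 30%. Uneven or lateral infection reaches further proximally for the same area and narrows the group; a plate wider at its distal end would widen it slightly.
- *The eligibility amendment made it worse.* It raised the upper limit from 50% to 75% and left the 20% floor alone. Under the same assumptions the exposed share fell, for example from 0.10/0.30 = 33% to 18% at 10 mm.
- *The comparison between groups is biased.* Allocation is randomised, so exposure should not differ systematically by group. In arms of about 13, chance imbalance is all that remains.

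**Conclusion.** The gap in the wording is real. A target nail with under 3 mm of distal involvement and 20% to under 30% of its area affected would, if fully cleared, succeed on the primary endpoint and fail the more lenient secondary one. The upper limit falls to 23.1% if the 30% is relative to baseline clear area, and the conflict disappears if it is relative to affected area.

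Under a full-width distal band it arises only in nails shorter than about 15 mm, so few patients are likely affected: none to about two of 39 on the illustrative assumptions above. The article gives neither nail lengths nor clearance rates, so the true number cannot be fixed. Severity: minor, as this is one secondary endpoint of a pilot.

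**What to change.** Before the month-6 analysis:

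1. Add a third route to secondary efficacy endpoint (a): complete clearance of the target nail when baseline distal involvement was below 3 mm. Do this by documented amendment or as a labelled sensitivity analysis beside the two-route result.
2. State the denominator of the 30%: total nail area, baseline clear area or baseline affected area.

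No new data should be needed: affected area and distance to the proximal fold are measured at enrolment (2.1), and affected area and nail length are assessed at follow-up (2.4). The cost is a late change to a secondary endpoint in an open-label trial whose enrolment is complete, and section 2 requires IRB-approved amendments for design changes. If month-6 results have already been seen, the labelled sensitivity analysis is the safer form.
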